**Figure 3 figure3:**
[figure not shown]
Iterative cocreation of Pregnant Faster. SES: socioeconomic status.

This research group has previously experienced difficulty in including women with a vulnerable health status in an interview study [34]. Although we believe that the nature of the intervention *Pregnant Faster* might encourage more women to participate, we consider these previously obtained experiences. Therefore, for this pilot study, we chose to aim for a sample size of 40 participants (10% of the larger planned cohort study), which we deemed sufficient to provide the first insights supporting further development of *Pregnant Faster*.

#### Participants

To be eligible, participants must meet all the following inclusion criteria: assigned female at birth, 18 to 45 years of age, living in the municipality of Rotterdam (the Netherlands), currently trying to conceive or planning to actively try within 3 months, or pregnant with a gestational age below 7+6 weeks, and having a vulnerable health status. In this study, having a vulnerable health status is defined as having a low SES based on the combination of a low to intermediate educational attainment (prevocational or vocational education) and living in a deprived neighborhood based on the zip code’s median income [36].

A potential participant who meets any of the following exclusion criteria will be excluded from participation in this study: insufficient proficiency in Dutch, not in possession of a smartphone or tablet suitable for the app, living outside of the municipality of Rotterdam, refusal to fill out the questionnaires, or refusal to participate in the interview.

The choice to only include citizens of the municipality of Rotterdam is based on the plan to deliver the rewards per bike, car, or public transport.

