**Figure 1 figure1:**
[figure not shown]
Generational impact of the vulnerable health status in women with a low socioeconomic status.

Most clinical manifestations of adverse pregnancy outcomes, such as hypertension or fetal growth restriction, are terminal features of a cascade of events that originate in the periconceptional period (ie, the 14 weeks before conception up to the first 10 weeks of pregnancy) [14]. During this period, on which the focus is limited in research as well as in clinical practice, modifiable poor lifestyle behaviors are known to be common risk factors for subfertility and adverse pregnancy course and outcomes [15-17]. For example, ≥80% of women who are contemplating pregnancy have at least one modifiable behavior associated with adverse pregnancy outcomes, such as not taking folic acid supplements, low vegetable and fruit intake, and smoking [18,19].

Preconception care (PCC) focuses on improving women’s health, including lifestyle behaviors, before pregnancy and plays an essential role in encouraging healthy lifestyle behaviors in preparation for pregnancy. Therefore, it reduces the risk of adverse pregnancy outcomes and improves health outcomes in mothers and their children now and later in life [20,21]. PCC is usually delivered face-to-face, for example, at midwifery practices or hospitals. However, web-based PCC has been gaining popularity, which are delivered through video consultations or even combined as blended care [22].

The low uptake of PCC by the general population in the Netherlands is associated with women’s perceived absence of risks and lack of awareness of PCC [23]. The delivery of PCC for women with a vulnerable health status faces even more obstacles, as these women are more difficult to reach and more difficult to motivate to engage in PCC [24]. These obstacles may lead to an ethically unjustifiable inequality in the health outcomes and life prospects of mothers and children from different socioeconomic backgrounds [24].

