### Cohort Study Protocol

#### Overview

This study was set up as an open cohort to reflect the real-life situation, and it aims to assess the feasibility of the mHealth app–based nudge that stimulates PCC uptake in women with an SES-related vulnerable health status.

After inclusion (T0), the women start the intervention, consisting of using the app daily. The total duration of the intervention will be 4 weeks per participant, as we deemed a short period of active engagement more feasible than a longer period and did not expect additional engagement in pregnancy preparation or PCC consultations after 4 weeks of using the app.

After the intervention (T1), participants fill out the “mHealth App Usability Questionnaire” (MAUQ), assessing the app, as well as partake in an interview in which they may state their opinions regarding the content of the app and how they rate their experience. At T1, we will assess the uptake of PCC as well (Figure 3). The results of this study will provide further insights to enhance the final design of the nudge and the app and can be viewed as another round in the iterative process, implementing the opinions and experiences of the target group into the final design. After this proposed cohort study, we aimed to update *Pregnant Faster* and plan to establish its effectiveness in a cohort of 400 women. Originally, the sample size of 400 was based on a power calculation for a randomized controlled trial with 2 groups using the app: one with and one without the allocation of rewards. However, the choice was made to convert the planned controlled trial to a cohort study due to the nature of this intervention and the possible disappointment women would feel if they would be randomized in a nonreward group, which could lead to disengagement and biased outcomes.

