#### Outcome Measures

The main objective of this study design is to establish the feasibility of the app *Pregnant Faster* as a nudge that encourages pregnancy preparation by stimulating the uptake of PCC. Feasibility in this study pertains to overall user satisfaction, the number of booked and visited PCC consultations, and the course of practical conduction with regard to the inclusion process, reward allocation, and finalization. The outcome will be assessed in multiple ways: (1) through the number of women who registered for this study, which indicates the effectiveness of the methods used to reach women; (2) the number of women eligible to participate, which indicates the effectiveness of these methods in reaching the target group; (3) the number of participants who were included and the number who actually started the intervention, which may reveal possible barriers between inclusion and conduction; (4) the number of participants completing the intervention, which offers information on how engaging the app is; and (5) the frequency with which certain rewards are chosen that indicates which rewards are deemed the most desirable and motivating. Furthermore, the usability of the app will be assessed using the MAUQ, a validated 18-item questionnaire on user satisfaction, information arrangement, and usefulness based on a 7-point Likert scale (strongly disagree, disagree, somewhat disagree, neither agree nor disagree, somewhat agree, agree, and strongly agree) as presented in Multimedia Appendix 1 [38].

To further investigate how participants have experienced using the app, the first 10 participants will be interviewed in a semistructured manner to explore the answers they give on questions such as how often they opened the app and if this was according to how often they would have liked to open the app. A topic list and additional information on this interview is present in Multimedia Appendix 2. This topic list and participants’ answers will be converted into a questionnaire offered to the remaining 30 participants. To include the first 10 participants in this questionnaire, the first author will fill in the questionnaire based on the participants’ answers in the interview. The MAUQ and the interview or additional questionnaire will be offered 4 weeks after a participant has started the intervention (T1).

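### Refusing the interview excludes any woman, yet only the first 10 of 40 participants are interviewed, so 30 places are screened on a procedure those women will not undergo.

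*Protocol article*

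**What the plan says.** Three parts of the cohort study protocol bear on who is interviewed.

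- **Participants.** A potential participant is excluded for "refusal to fill out the questionnaires, or refusal to participate in the interview". The criterion is not restricted to any subset.
- **Overview.** At T1, participants in general complete the mHealth App Usability Questionnaire (MAUQ) and "partake in an interview in which they may state their opinions".
- **Outcome Measures.** Here "the first 10 participants will be interviewed in a semistructured manner", and the topic list and their answers are "converted into a questionnaire offered to the remaining 30 participants". The Abstract likewise speaks of interviews or questionnaires.

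On the target group, the Introduction states that "these women are more difficult to reach and more difficult to motivate to engage in PCC". The sample size paragraph in the Overview, after the Figure 3 caption, adds that the research group "previously experienced difficulty in including women with a vulnerable health status in an interview study". Outcome Measures lists the number registered (1), the number eligible (2), the numbers included and started (3), the number completing (4) and the rewards chosen (5). It reads the number eligible as a sign of how well recruitment reaches the target group.

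**The concern.** An eligibility rule should match the procedures that a participant will undergo. Here the rule and the Overview treat the interview as common to everyone, while Outcome Measures limits it to a quarter of the cohort. For the other three quarters, a woman could be turned away for declining something that she would never be asked to do.

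This matters more than usual because recruitment flow is itself an outcome. A woman with the right age, address, education and pregnancy intention who declines an interview becomes ineligible. The number eligible then mixes two things: whether the flyers, practices and social media reached the right women, and whether those women dislike interviews. The rule may also tilt the cohort towards more willing women, although the design was chosen to reflect real life and the 400-woman continuation depends on what the pilot shows.

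**Working it through.** **Inputs from the article.** Planned cohort 400; pilot 40, as "sample size of 40 participants (10% of the larger planned cohort study"; 10 interviewed; 30 given the questionnaire. The article gives no refusal rate and no expected completion or uptake rate.

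**1. The plan's own figure.** 0.10 × 400 = 40, and 10 + 30 = 40. The sample size and its split reproduce.

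**2. Share of places where the interview criterion has no purpose.** 30 / 40 = 75%. Willingness is required for 100% of places and used in 10 / 40 = 25%.

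**3. Extra screening (assumed refusal share r).** If the rule applies to all places, filling 40 needs 40 / (1 − r) otherwise eligible women, an increase of 1 / (1 − r) − 1. If it applies only until 10 interviews are secured, the expected need is 10 / (1 − r) + 30.

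| r (assumed) | Rule on all 40 places | Increase | Rule on 10 places only |
|---|---|---|---|
| 10% | 40 / 0.9 = 44.4, so 45 | 11% | 11.1 + 30 = 41.1 |
| 20% | 40 / 0.8 = 50 | 25% | 12.5 + 30 = 42.5 |
| 40% | 40 / 0.6 = 66.7, so 67 | 67% | 16.7 + 30 = 46.7 |

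**4. Possible overstatement of a completion or uptake rate.** Let p be the rate in women who accept the interview and q the rate in those who refuse. All otherwise eligible women together have the rate (1 − r)p + rq, so a cohort of accepters overstates it by r(p − q).

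- If refusers do not differ (q = p): 0 at every r.
- If q = p/2 and p = 0.5: 0.10 × 0.25 = 2.5 points at r = 10%, and 0.40 × 0.25 = 10 points at r = 40%.
- If q = p/2 and p = 0.8: 0.10 × 0.40 = 4 points at r = 10%, and 0.40 × 0.40 = 16 points at r = 40%.

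Here r, p and q are all assumptions. The halved rate in refusers only illustrates how the formula behaves; nothing in the article supports or excludes it.

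**5. Which outcomes the rule can touch.** Registration happens when a woman enters her email address, before the screening survey, so outcome (1) is unaffected. Outcomes (2) and (3) can fall directly. Completion and uptake of preconception care can shift only if refusers behave differently. App use, reward choices, consultation requests and confirmed visits can all be recorded without an interview.

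**The case against.** The strongest reply is that the specific section governs. Outcome Measures is clear, the Abstract agrees with it, and the Overview is only a summary. A woman who enters after the tenth may never be asked about an interview, and then she cannot refuse one. The Recruitment and Inclusion section describes a screening survey on the inclusion criteria and mentions no question on interview willingness. This reading is possible, but no section states it, and the exclusion as written covers any potential participant. The reply shows that the harm may not occur in practice; it does not make the text consistent.

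There is also a sound reason to ask early entrants. It may not be known at screening who will be among the first 10, and their answers shape the later questionnaire. That stands, but the reason ends once 10 interviews are secured.

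The reported recruitment difficulty concerned a stand-alone interview study, and the authors expect this intervention to attract more women. It makes interview refusal plausible here but does not give a rate.

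A reader might go further in four ways that the article does not support:

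- **That the questionnaire exclusion is equally needless.** All 40 are due the MAUQ, and user satisfaction is part of feasibility. Requiring agreement to it is a defensible choice.
- **That non-response is removed.** Agreeing at entry does not guarantee a T1 response four weeks later, and included, started and completed are counted separately.
- **That feasibility is measured only in the most compliant women.** Refusal at entry is one filter, of unknown strength.
- **That 90% T1 response among accepters with 20% refusal means 0.90 × 0.80 = 72% overall.** This assumes that no woman who declines an interview would return a questionnaire. If they responded equally, the figure would stay at 90%.

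**Conclusion.** The point holds for the interview criterion. The Participants and Overview sections do not match Outcome Measures, and as written 75% of places are screened on a procedure that does not apply to them. That share is exact.

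The consequences are conditional. The rule can lower the numbers eligible and included for a reason unrelated to reach, and it may select somewhat more willing women. The amount cannot be determined from the article. The 11% to 67% of extra screening rests on assumed refusal of 10% to 40% and on the rule being enforced for every place. The effect on completion or uptake ranges from zero upwards, depending on whether refusers differ. This is an avoidable filter that should be corrected; it does not invalidate the pilot.

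**What to change.** 1. In Participants, delete refusal of the interview as an exclusion, or state that it applies only until the 10 interviews are secured. Keep the questionnaire-refusal exclusion if wished.
2. In the Overview, say that participants complete the MAUQ and either an interview (first 10) or the additional questionnaire, to match Outcome Measures.
3. In the recruitment flow, count women lost through interview refusal and through questionnaire refusal, each separately from women outside the target group, so that the number eligible can be read as a measure of reach.

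The cost is one eligibility line, one overview sentence and two extra counts; the sample size stays at 40. If the interview becomes optional, the 10 interviewed women are partly self-selected, and their answers shape the questionnaire given to the rest. Reporting how many were invited before 10 accepted would show how far this went. Keeping the rule for the interview places avoids women declining within the cohort, but it leaves the selection in those 10 places.

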#### Recruitment and Inclusion

Women from the target population will be recruited not only through midwifery practices, hospitals, and general practitioner practices but also directly through the distribution of flyers and posters and through social media, specifically Instagram and Facebook. Social media campaigns will be directly targeted at specific areas and populations, which fit our inclusion criteria. Recruitment will take place in collaboration with the Regional Consortium Pregnancy & Childbirth of the Southwest Netherlands, in particular with 5 midwifery practices located in or near deprived neighborhoods of Rotterdam. Women may enroll themselves in the study or they can be enrolled by a health care provider.

When women receive the flyer or are informed about the study by a health care provider, they may fill in their email on the website *Getting Pregnant Faster* [37]. The researcher receives their email address and sends them a screening survey with questions regarding the inclusion criteria. This information will allow for the selection of women who fit the target group. If a potential participant is eligible, the researcher will contact her via telephone and email to provide further information about the study. If the woman is interested in participating, informed consent will be sent via email.

If women are eligible and have signed the informed consent form, they will be asked to download the app and start the intervention. If women are not eligible for participation, they will be provided with a free 26-week subscription to our mHealth coaching platform *Smarter Pregnancy*.

#### Randomization and Blinding

Owing to the nature of the intervention, all participants will receive the same intervention. Therefore, this section is not applicable. Blinding of the participants is not possible. Neither the participants nor the researchers will be blinded.

#### Intervention

The intervention consists of using the app *Pregnant Faster* (Dutch: *Sneller Zwanger*), which can be viewed as a macrolevel nudge containing a multitude of microlevel nudges. All nudges are aimed at encouraging participants to adequately prepare for pregnancy by making healthy nutrition and lifestyle choices and visiting a PCC consultation.

#### Outcome Measures

The main objective of this study design is to establish the feasibility of the app *Pregnant Faster* as a nudge that encourages pregnancy preparation by stimulating the uptake of PCC. Feasibility in this study pertains to overall user satisfaction, the number of booked and visited PCC consultations, and the course of practical conduction with regard to the inclusion process, reward allocation, and finalization. The outcome will be assessed in multiple ways: (1) through the number of women who registered for this study, which indicates the effectiveness of the methods used to reach women; (2) the number of women eligible to participate, which indicates the effectiveness of these methods in reaching the target group; (3) the number of participants who were included and the number who actually started the intervention, which may reveal possible barriers between inclusion and conduction; (4) the number of participants completing the intervention, which offers information on how engaging the app is; and (5) the frequency with which certain rewards are chosen that indicates which rewards are deemed the most desirable and motivating. Furthermore, the usability of the app will be assessed using the MAUQ, a validated 18-item questionnaire on user satisfaction, information arrangement, and usefulness based on a 7-point Likert scale (strongly disagree, disagree, somewhat disagree, neither agree nor disagree, somewhat agree, agree, and strongly agree) as presented in Multimedia Appendix 1 [38].

To further investigate how participants have experienced using the app, the first 10 participants will be interviewed in a semistructured manner to explore the answers they give on questions such as how often they opened the app and if this was according to how often they would have liked to open the app. A topic list and additional information on this interview is present in Multimedia Appendix 2. This topic list and participants’ answers will be converted into a questionnaire offered to the remaining 30 participants. To include the first 10 participants in this questionnaire, the first author will fill in the questionnaire based on the participants’ answers in the interview. The MAUQ and the interview or additional questionnaire will be offered 4 weeks after a participant has started the intervention (T1).

The number of PCC consultation requests and confirmed visits will be registered during the study period and in the aforementioned questionnaires, women will be asked why they registered (or did not register) for a PCC consultation and if they changed their lifestyle behaviors due to using the app. Descriptive statistics will be used for these outcomes, and the results will be reported in a narrative and tabular form.

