Another microlevel nudge lies in the varying value of the coins. One coin represents a monetary value of €0.06 to €0.26 (US $0.06 to US $0.26). By making healthy rewards, such as folic acid supplements and fruits, relatively cheap, we steer participants toward picking healthy products over luxury goods, while still allowing them to choose luxury goods if that is what stimulates them most to earn coins and engage in PCC. For instance, the mascara and folic acid supplements are of equal monetary value and cost €3.00 (US $3.00). However, the folic acid supplements can be ordered for 10 coins whereas ordering the mascara will cost the participant 35 coins.

Participants of our previously conducted interview study [34] mentioned that it might be painful for them if they could only choose pregnancy and baby-related products, in case of not getting pregnant quickly. To take this into account, we have included rewards in the app that are not relatable to pregnancy or babies, such as water bottles, a book voucher, and resistance bands for physical exercise.

The design of *Pregnant Faster* makes the app suitable for all women because it automatically matches participants’ personal preferences and their current level of motivation to prepare for pregnancy and engage in PCC. This is done by allowing participants to freely choose the type and timing of their rewards and by matching their current “Stage of Change,” as described by Prochaska and DiClemente [39].

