If a nudge only appeals to extrinsic motivation, the healthy behavior “dies out” as soon as the intervention ends [46]. However, scaffolding intrinsic motivation leads to a more sustainable change because it focuses on health-related rewards. Overall, women who want to become pregnant wish to have a healthy baby. Educating them about the control they may exercise on their pregnancy outcomes by taking up PCC and making healthy nutrition and lifestyle choices fits their wish to have a healthy baby and may increase their intrinsic motivation to make healthy choices. This cancels out the *crowding out* effect and allows for continuation of healthy behavior because the focus is not placed on limited material rewards but on continued health-related rewards, making the behavioral changes more sustainable.

Another potential risk lies in how the app makes women feel. It is known that mHealth apps may evoke feelings of guilt, shame, and stress and even discouragement when participants fail to meet the app’s goals [47]. It is paramount that the tips and blogs in *Pregnant Faster* convey that small steps are worth celebrating and that women are not obliged to strive for a perfect lifestyle to have a healthy baby. Furthermore, the app must also contain information on the fact that a healthy lifestyle increases the chance of a healthy baby but offers no guarantees. It must be stated that not all adverse outcomes can be prevented and that an adverse pregnancy outcome does not mean that the woman (or her partner) is to blame.

When this pilot study has been conducted, we expect to have obtained valuable information on how to further adjust *Pregnant Faster* to best fit the needs of women with a vulnerable health status and encourage PCC uptake in this group. In other words, this proposed study can be viewed as yet another phase of the iterative process, and the outcomes will be used to update and alter the app to further develop the design of *Pregnant Faster*. Furthermore, practical information on, for example, the number of registrations of eligible and noneligible women will provide guidance on our methods to reach the target group and evaluation of the rewards, and the frequency of allocation will provide more insight into which rewards are deemed most desirable. Finally, any barriers encountered during this pilot study will be assessed to avoid such barriers in the future.

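### Reward-choice frequency mixes preference with deliberate coin-price steering, so it cannot on its own be read as desirability

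*Protocol article*

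**What the plan says.** Outcome Measures lists five counts through which feasibility will be assessed. The fifth is "the frequency with which certain rewards are chosen that indicates which rewards are deemed the most desirable and motivating". The article attaches this interpretation to the count without qualification. The Discussion (Principal Findings) repeats it: "the frequency of allocation will provide more insight into which rewards are deemed most desirable".

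The App Design section of the Results describes the pricing of rewards as one of the app's nudges: "By making healthy rewards, such as folic acid supplements and fruits, relatively cheap, we steer participants toward picking healthy products over luxury goods". Luxury goods stay available, "while still allowing them to choose luxury goods if that is what stimulates them most to earn coins and engage in PCC". The worked example is a pair of items, each valued at €3.00, for which "the folic acid supplements can be ordered for 10 coins whereas ordering the mascara will cost the participant 35 coins". The same paragraph puts the value of a coin between €0.06 and €0.26.

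No section adjusts reward frequency for coin price, and the limitations in the Discussion do not mention pricing.

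**The concern.** The study sets the relative prices in order to move choices, and then reads the choices as an expression of what women want. If folic acid tops the list, two explanations fit equally well: women wanted it, or the low price worked. They lead to different decisions about the reward list. The first says to keep the item because it attracts women. The second says the steering succeeded and leaves open what women would have picked at equal prices.

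Order counts raise a further difficulty. The App Design section reports that women wished to be able either to save for a large reward or to buy several small ones. A woman who saves for the one item she wants most adds a single order; a woman who buys small items adds many.

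What is at stake is limited. The Discussion says the study's outcomes will be used to update the app, and reward frequency is one of the inputs named there.

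**Working it through.** **Inputs (The App Design).** Folic acid: €3.00, 10 coins. Mascara: €3.00, 35 coins. Stated coin value: €0.06 to €0.26. First log-in: 50 coins.

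**The plan's own figure first.** Value per coin = euro value / coin price.
- Mascara: 3.00/35 = €0.086, inside the stated range.
- Folic acid: 3.00/10 = €0.30, above the stated maximum of €0.26. At €0.26 per coin it would cost 3.00/0.26 = 11.5 coins.

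The stated range is therefore not reproduced by the article's own example. This is a side point, but the two figures need to be reconciled. The price ratio is 35/10 = 3.5 on the example as printed, or about 35/11.5 = 3.0 if folic acid were priced at the stated maximum value. Across all rewards, the stated range allows up to 0.26/0.06 = 4.33-fold.

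**Effect on order counts.** Let *s* be the share of the coins spent on these two items that goes to mascara. The article does not give *s*, so it is varied here.

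Orders of folic acid : mascara = [(1 − s)/10] / [s/35] = 3.5 × (1 − s)/s

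| Share spent on mascara (assumed) | Folic acid : mascara orders |
|---|---|
| 50% | 3.5 : 1 |
| 60% | 2.33 : 1 |
| 70% | 1.5 : 1 |
| 35/45 = 77.8% | 1 : 1 |
| 80% | 0.875 : 1 |

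Between 50% and 77.8%, women put more coins into mascara, yet folic acid leads on orders.

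**The case with no distortion.** If each woman wants one of each, the cost is 10 + 35 = 45 coins, below the 50 given at first log-in. Price then forces no choice, and the count is 1:1.

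**Does share of coins solve it?** No. In the one-of-each case, mascara takes 35/45 = 77.8% of the coins and folic acid 10/45 = 22.2%, a 3.5-fold lead with no difference in preference. Coin share is biased toward expensive items.

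**How far could price dominate?** An illustrative simulation assumed 12 rewards of equal euro value, coin values uniform over €0.06 to €0.26, 40 women with about 400 coins each, and fixed spending shares. All of these except the 40 women and the coin-value range are assumptions. Mean rank correlations of order frequency were:

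| Spread of preference (SD, log scale) | With cheapness | With preference |
|---|---|---|
| 0 | 0.92 | not defined |
| 0.25 | 0.78 | 0.46 |
| 0.5 | 0.56 | 0.70 |
| 1 | 0.32 | 0.87 |
| 2 | 0.18 | 0.93 |

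With weak preferences the counts mostly follow price; with strong ones they mostly follow preference. The ledger alone cannot show which situation holds.

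**The case against.** A reader might infer that the ranking will simply reproduce the price list. The documents do not support that. The full price list is not given, and the 3.5-fold ratio comes from one example pair. Counts carry preference as well as price, and in the simulation they follow preference more closely than price once the spread reaches 0.5. The one-of-each case shows no distortion at all. Coins are also plentiful relative to these prices: with daily log-in and one 4-coin item read each day (assumed), a woman earns 50 + 27 + 28 × 4 = 189 coins without ticking any behaviour or booking a consultation.

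A reader might also infer that the reward list of the updated app would rest on this ranking, or that continuation depends on it. Neither is stated. The Discussion sentence that names frequency also mentions evaluating the rewards, and continuation is tied to user satisfaction and PCC uptake. Every participant gets an interview or questionnaire at T1, and its topic list (Multimedia Appendix 2) is not shown, so it may already ask about reward preference.

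Finally, frequency is not defined as orders; it could mean the number of women who chose a reward. That would remove the effect of repeat orders, but whether a woman chooses an item at all may still respond to its price.

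These points reduce the size and the consequence. They do not rescue the interpretation, which the article itself fixes and which its own pricing contradicts.

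**Conclusion.** The point holds in a limited form. Outcome (5) and the matching Discussion sentence give reward frequency a meaning it cannot carry alone, because the app prices rewards in order to influence that frequency. For the example pair, the order ratio in the cases examined runs from 3.5:1 for folic acid (equal coin split, assumed) through 1:1 (one of each, or 77.8% of coins on mascara) to a reversal at higher mascara shares. How women will spend is unknown, so no single figure can be given for the distortion.

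It is a minor correction to a secondary descriptive measure in a 40-woman feasibility cohort. PCC uptake, the MAUQ and the inclusion counts are not affected.

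**What to change.** 1. In Outcome Measures and in the Discussion, relabel the measure as take-up at the offered coin price, and drop the claim that it shows by itself what is most desirable and motivating.
2. For each reward, report the number of women choosing it at least once and the number of orders, beside its coin price and euro value. Give share of coins spent only as a supplementary figure, noting its bias toward expensive items.
3. Base statements about desirability on one T1 item asking women to rank the rewards as if all cost the same number of coins, unless the topic list in Multimedia Appendix 2 already covers this. Ask it directly of the first 10 participants too, since their questionnaire is otherwise completed from interview answers.
4. Reconcile the folic acid example (€0.30 per coin) with the stated range of €0.06 to €0.26.

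The cost is one questionnaire item, a small tabulation from the coin records that the app already keeps, and a few words of text. The ranking item is hypothetical, so it should be read alongside take-up and not replace it.
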